Axillary ultrasound, the most used imaging modality for nodal assessment, is an unreliable staging modality for BC patients with a low nodal metastatic burden; its negative predictive value (60% to 90%) is not reassuring [5,6,7,8,9]. Different rates of sensitivity and specificity of axillary ultrasound are reported in the literature, ranging from 26% to 94% and from 53% to 98%, respectively [7,8,9,10,11]. Thus, for most BC patients presenting with a clinically and radiologically node-negative axilla at diagnosis, in the quest to reliably stage the axilla, the surgical sentinel-node procedure is routinely used for staging [12]. However, for BC patients aged >70 years with hormone-receptor-positive and human epidermal growth factor receptor 2 (HER2)-negative conditions, sentinel-lymph-node surgery is optional if the patient receives adjuvant endocrine therapy according to ASCO guidelines [12]. However, these guidelines are not implemented in Sweden, and the surgical management of the axilla is the same, independent of age at diagnosis and molecular subtype. In the majority (~80%) of early BC patients undergoing sentinel-node surgery, the procedure identifies only healthy lymph nodes with no metastatic tumor deposits [3,4]. For these patients, the invasive surgical procedure is diagnostic but not therapeutic.

Although there are many benefits of the minor surgical sentinel-node procedure compared to axillary dissection, sentinel-node surgery is associated with short- and long-term side effects. Most importantly, immediate postoperative swelling, paresthesia, arm lymphedema, and self-reported symptoms of arm swelling are documented complications of the sentinel-node procedure [13,14]. In addition, the procedure is time-consuming and requires financial healthcare resources.

We previously developed and published a decision-making tool, the noninvasive lymph node staging (NILS) prediction model, for the prediction of benign lymph nodes in primary BC [15]. The NILS prediction model, which is an artificial neural network (ANN) model, was developed using retrospectively collected variables (including patients, *n* = 800). The NILS prediction model includes ten top-ranked risk variables for nodal status (please refer to Section 2.1), including hormone receptor status but excluding molecular subtype. The aim of this study is to retrospectively validate the NILS prediction model in one temporal and one geographical cohort.

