### 2.6. Power Calculation and Statistical Plan

We estimated that the sample size would be *n* = 300 study participants, and although each validation cohort will be assessed separately, the total number would be *n* = 600. Due to practical reasons (shortage of qualified research personnel at one of the study sites), we will include *n* = 400 from the temporal cohort and *n* = 200 from the geographical cohort. The area under the curve (AUC) for the original prediction model was 0.74 in a development cohort, where two-thirds of the patients were node-negative [15]. Assuming the same proportion of N0 and the same discrimination for future patients, the inclusion of 300 patients is sufficient to obtain 90% probability of reaching an AUC of at least 0.70 in this validation study. This calculation was based on the asymptotic normality of the AUC estimate and simulations that determined the relationship between the sample size and standard error of the AUC estimate. The performance of the ANN decision tool upon validation will be assessed in terms of discrimination (AUC) and calibration (comparison of the observed and predicted event rates of benign axillary nodal status, Hosmer–Lemeshow test). Separate analyses of patients undergoing breast-conserving surgery and mastectomy will be performed. No interim analyses will be performed. Patients will be screened for eligibility according to specified inclusion and exclusion criteria and subsequently included if all criteria are fulfilled. Study participants for whom mandatory variables for the NILS protocol are missing, i.e., variables that the ANN model cannot predict, will be excluded.

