### 2.7. Inclusion Criteria

The inclusion criteria are:Accepted study participation (e.g., did not opt out);Female sex;Invasive BC;Negative preoperative assessment of the axilla, clinically and by ultrasound;Scheduled for primary surgery.

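### The single 90% in Section 2.6 rests on n = 300 and two-thirds N0; the 200-patient cohort has about 85%, or about 81% at the Introduction's N0 share.

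*Protocol article*

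**What the plan says.** Section 2.6 of the protocol article takes its inputs from the model's development: "The area under the curve (AUC) for the original prediction model was 0.74 in a development cohort", "where two-thirds of the patients were node-negative". It carries both to the validation study ("Assuming the same proportion of N0 and the same discrimination for future patients") and concludes that "the inclusion of 300 patients is sufficient to obtain 90% probability of reaching an AUC of at least 0.70". On method it says: "This calculation was based on the asymptotic normality of the AUC estimate and simulations".

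The 300 is a per-cohort figure, since the section adds "although each validation cohort will be assessed separately" and gives a total of 600. It then sets 400 patients for the temporal cohort (Malmö) and 200 for the geographical cohort (Helsingborg), because of a staff shortage at one site. The probability is not restated for these sizes.

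The Introduction gives a different N0 share: "In the majority (~80%) of early BC patients undergoing sentinel-node surgery, the procedure identifies only healthy lymph nodes". Section 2.7 requires "Negative preoperative assessment of the axilla, clinically and by ultrasound". Section 2.8 excludes patients without surgical axillary staging and those with upfront axillary dissection. What remains is essentially a sentinel-node population.

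**The concern.** The stated probability depends on two planning inputs that the rest of the document does not bear out.

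- **Cohort size.** No cohort has 300 patients.
- **N0 share.** The protocol motivates the study with about 80% N0 in sentinel-node patients but sizes it with two-thirds. It neither explains the choice nor shows how sensitive the result is to it. The precision of an AUC depends heavily on the smaller class, here N+, which would fall from 33% to 20% of patients.

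A reader who takes 90% as the property of each separate assessment would expect too much of the geographical cohort, the only test at a different kind of site. The N0 share also bears on the secondary endpoint (Section 2.9.2), a false-negative rate of at most 10%, because its denominator is the number of N+ patients.

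**Working it through.** **Inputs.** True AUC 0.74, target 0.70, N0 share 2/3, n = 300 and probability 90% (Section 2.6); cohort sizes 400 and 200 (Section 2.6); N0 share about 80% (Introduction).

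**Step 1: reproduce the plan's figure.** With a normally distributed AUC estimate, P = Φ((0.74 − 0.70)/SE). At n = 300 with 200 N0 and 100 N+:

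- Hanley–McNeil, N+ as the positive class: SE 0.0319, P = 89.5%
- Hanley–McNeil, classes swapped: SE 0.0285, P = 92.0%
- Obuchowski binormal variance: SE 0.0329, P = 88.8%
- Equal-variance binormal simulation: SE 0.0302, P = 90.8%

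The stated 90% is confirmed to within about 2 points.

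**Step 2: recover the SE that the plan implies.** 0.04/1.2816 = 0.0312 at n = 300 and p = 2/3, where p is the N0 share.

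**Step 3: scale it to the actual cohorts.** SE is taken as proportional to √(1/N0 + 1/N+), that is, to 1/√(n·p·(1 − p)). The reference value is 300 × 2/3 × 1/3 = 66.67, so SE = 0.0312 × √(66.67/(n·p·(1 − p))).

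| n | N0 share | n·p·(1 − p) | SE | 0.04/SE | P | Range over the four methods in Step 1 |
|---|---|---|---|---|---|---|
| 300 | 2/3 | 66.67 | 0.0312 | 1.28 | 90.0% | 88.8–92.0% |
| 300 | 80% | 48 | 0.0368 | 1.09 | 86.2% | 84.4–89.6% |
| 200 | 2/3 | 44.44 | 0.0382 | 1.05 | 85.2% | 84.0–87.4% |
| 200 | 75% | 37.5 | 0.0416 | 0.96 | 83.2% | 81.6–86.2% |
| 200 | 80% | 32 | 0.0451 | 0.89 | 81.3% | 79.5–84.8% |
| 400 | 2/3 | 88.89 | 0.0270 | 1.48 | 93.1% | 92.0–94.8% |
| 400 | 75% | 75 | 0.0294 | 1.36 | 91.3% | 89.9–93.9% |
| 400 | 80% | 64 | 0.0319 | 1.26 | 89.5% | 87.9–92.7% |

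**Step 4: split the loss at n = 200.** From 90.0% to 85.2% (about 5 points) is cohort size alone. From 85.2% to 81.3% (about 4 points) is the N0 share.

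**Step 5: expected N+ patients.**

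- n = 200: 200/3 = 67 at two-thirds N0; 200 × 0.20 = 40 at 80% N0.
- n = 400: 400/3 = 133 at two-thirds N0; 400 × 0.20 = 80 at 80% N0.

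Either way the count falls by 40%. To illustrate with observed rates near the 10% limit, 4 of 40 missed has an exact 95% interval of 2.8–23.7%, and 7 of 67 missed has 4.3–20.3%.

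**The case against.** **The calculation is not wrong.** A reader might infer an arithmetic mistake. There is none: the 90% follows from its inputs, and the two-thirds share is openly labelled as an assumption. This stands. The fault is a planning input that disagrees with another figure in the same document.

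**About 80% is a background figure.** It is approximate, cited from the literature, and not an observed rate at either hospital. Two-thirds comes from the investigators' own development cohort. The inclusion criteria set no tumour-size limit, and mastectomy patients are analysed too. Whether the development cohort was itself clinically node-negative cannot be seen from this document. This also stands, so 80% is one end of a range and not an established value.

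**The enrolled patients might seem likely to exceed 80% N0**, because negative clinical and ultrasound findings are required. The text does not support this. The Introduction describes sentinel-node surgery as routine for patients who are already clinically and radiologically node-negative, so that selection is largely contained in the 80%.

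**The N0 effect is modest.** At n = 300 it is about 4 points, against a spread of about 5 points between variance methods, and the 400-patient cohort stays near 90%. This stands for those two sizes. It does not rescue the 200-patient cohort, which is below 90% at both N0 shares and below 85% at 80% N0 under every method tried.

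**Three further inferences go beyond the plan.**

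- A joint probability that both cohorts reach 0.70 answers a question the protocol does not ask, since no such criterion is stated.
- A pooled analysis of 600 is no remedy within the plan, because the cohorts are to be assessed separately.
- A different N0 share does not show that the model will be miscalibrated. The document gives no mean prediction for these patients, and measuring calibration is one of the study's aims.

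**Conclusion.** Wrong as written, of minor to moderate weight: the stated 90% rests on planning inputs that do not match the cohorts. For the geographical cohort the probability is about 85% at two-thirds N0 and about 81% at 80% N0. For the temporal cohort it is about 93% and about 90%, so the shortfall lies mainly with the smaller cohort. It would be an overstatement to put the whole drop from 90% to 81% down to the N0 share, since slightly more than half of it is cohort size.

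These figures assume a true AUC of 0.74, as the protocol does, a normally distributed AUC estimate, and a standard error that scales with the class sizes as shown. The direction is secure. The exact percentages move by a few points with the variance formula.

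**What to change.** In Section 2.6, replace the single 90% with the probability of an observed AUC of at least 0.70 for each actual cohort, n = 400 and n = 200, over an N0 share of 67–80%. Recompute it with the protocol's own simulated standard errors. By the scaling above, the entries would run from about 93% down to about 90% for the temporal cohort, and from about 85% down to about 81% for the geographical cohort. Give the expected N+ counts alongside (133 to 80, and 67 to 40), since they also govern the precision of the false-negative rate.

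Then either reconcile the two-thirds assumption with the Introduction's figure, or state why the development cohort's share is the better guide for these two hospitals.

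The cost is wording only: no extra patients, data or analyses. The stated probability becomes slightly less favourable.

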## 2. Materials and Methods

### 2.1. Study Design

This validation study of the NILS prediction model will be a multicenter, retrospective study based on prospectively collected clinicopathological variables included in patients’ medical charts, mammograms, and pathology reports. We plan to assess the external validity and model validity of the NILS prediction model for healthy lymph nodes and evaluate the discrimination and calibration of the NILS prediction model while following the TRIPOD statement [16]. A schematic schedule of enrollment, data collection, and monitoring is provided in Figure 1. This study aims to validate the NILS prediction model, a previously published ANN-based decision-making tool that is based on retrospectively collected data at Lund University Hospital, Sweden. In agreement with TRIPOD recommendations, the data in this validation study are derived from cohorts different in both time and study sites. Thus, patients who underwent surgery for primary BC in Malmö, Sweden, in 2020 (*n* = 400, a temporal validation cohort) and in Helsingborg, Sweden, between 2019 and 2020 (*n* = 200, a geographical external validation cohort) will be identified by a national registry of cancer diagnoses, treatments, and outcomes (INCA). The data retrieved from clinical files will include age at BC diagnosis, medical history of BC, ultrasound assessment of the axilla, and clinical status of the axilla. Tumor size and localization in the breast, including laterality, multifocality, and mode of tumor detection, will be obtained from imaging assessment reports (mammography, followed by ultrasound assessment in cases of an inconclusive mammographic report). In cases where multifocality is detected by either clinical examination or any imaging modality in this study, the tumor will be considered multifocal. Tumor biology data (estrogen receptor status, progesterone receptor status, HER2 status, molecular and histopathological subtype, vascular invasion, and proliferation index Ki-67) will be obtained using preoperative core needle biopsy. Number of metastatic axillary lymph nodes will be obtained from reports of surgical pathology specimens (sentinel-node surgery and axillary dissection).

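### Section 2.6 gives a 90% probability for 300 patients per cohort, but the cohorts are 400 and 200; on the plan's own assumptions the 200-patient geographical cohort has about 85–87%

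*Protocol article*

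**What the plan says.** All of the relevant text except the confirmation of cohort sizes is in Section 2.6 (Power Calculation and Statistical Plan) of the protocol article.

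- **Intended size.** "We estimated that the sample size would be *n* = 300 study participants, and although each validation cohort will be assessed separately", and then "the total number would be *n* = 600". Two cohorts of 300 make 600, so 300 is the size for one cohort.
- **Actual size.** "we will include *n* = 400 from the temporal cohort and *n* = 200 from the geographical cohort". The reason given is a "shortage of qualified research personnel at one of the study sites". Section 2.1 (Study Design) repeats both sizes, including 200 for Helsingborg.
- **Operating characteristic.** After the change of split, the only probability given is that "the inclusion of 300 patients is sufficient to obtain 90% probability of reaching an AUC of at least 0.70 in this validation study". It assumes the development-cohort AUC of 0.74 and two-thirds node-negative patients. It rests on a normal approximation, with the standard error taken from simulations over sample size.

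No probability is given for 200 or for 400 patients.

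**The concern.** A sample-size statement should describe the analyses that will be done. Here the 90% is attached to a cohort of 300, while the planned cohorts have 400 and 200 patients and are to be assessed one by one. The geographical cohort has two-thirds of the size behind the figure, and under separate assessment the extra patients at Malmö do not make its AUC more precise.

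What is at stake is how a disappointing result at Helsingborg would be read. This is the cohort that Section 2.1 labels geographical and external. A reader who carries the 90% over to it would think that an observed AUC below 0.70 has a 10% chance when the model performs exactly as assumed. The actual chance is about 13–15%.

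**Working it through.** **Inputs (all from Section 2.6).** True AUC 0.74; target 0.70 for the observed AUC; node-negative share 2/3; stated probability 0.90 at n = 300; actual sizes 200 and 400.

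**Formula.** P(observed AUC ≥ 0.70) = Φ((0.74 − 0.70)/SE) = Φ(0.04/SE).

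**Step 1: reproduce the plan's figure at n = 300 (200 N0, 100 N+).**
- Binormal simulation, 20,000 runs: SE 0.0302, giving 90.8% by the normal approximation and 90.3% as the simulated proportion.
- Hanley–McNeil, SE² = [A(1−A) + (n₁−1)(Q₁−A²) + (n₀−1)(Q₂−A²)]/(n₁n₀), with Q₁ = A/(2−A), Q₂ = 2A²/(1+A), and n₁ the number in the class treated as the event. With metastatic as the event, SE 0.0319 and 89.5%; with benign as the event, SE 0.0285 and 92.0%.

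The stated 90% is therefore sound for 300 patients.

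**Step 2: scale the plan's own standard error.** The stated 90% implies SE = 0.04/1.2816 = 0.0312 at n = 300. With the node-negative share fixed, SE scales with 1/√n.
- n = 200: SE = 0.0312 × √(300/200) = 0.0382; Φ(0.04/0.0382) = 85.2%.
- n = 400: SE = 0.0312 × √(300/400) = 0.0270; Φ(0.04/0.0270) = 93.1%.

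**Step 3: check by the other methods.**

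| Method | n = 200 | n = 300 | n = 400 |
|---|---|---|---|
| Plan's implied SE, scaled | 85.2% | 90% (stated) | 93.1% |
| Simulation, normal approximation | 86.2% | 90.8% | 93.8% |
| Hanley–McNeil, metastatic as event | 84.7% | 89.5% | 92.6% |
| Hanley–McNeil, benign as event | 87.4% | 92.0% | 94.8% |

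At n = 200 the range is 84.7–87.4%, which is 2.6 to 5.3 points below 90%.

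**Step 4: both cohorts.** The cohorts hold different patients, so their estimates are taken as independent. At 200 and 400: 0.852 × 0.931 = 0.793. At 300 and 300: 0.90 × 0.90 = 0.81. The change of split costs less than 2 points.

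**Step 5: expected precision.** 95% half-width = 1.96 × SE: 1.96 × 0.0382 = 0.075 at n = 200; 1.96 × 0.0312 = 0.061 at n = 300; 1.96 × 0.0270 = 0.053 at n = 400.

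**Sensitivity only.** The Introduction gives about 80% node-negative among early breast cancer patients undergoing sentinel-node surgery. With that share in place of two-thirds, n = 200 gives about 80–85% over the simulation and the two Hanley–McNeil variants. This is not the assumption on which the plan's calculation rests.

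**The case against.** The best defence is that nothing in Section 2.6 is false. The 90% is stated for 300 patients and reproduces. The unequal split, its allocation and its reason are all disclosed, so any reader can see that 200 is less than 300. This stands in part: the calculation is correct, and the fault is that its result was not carried through to the sizes actually planned. Disclosing the split does not disclose its consequence.

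Several stronger readings are tempting, and the document does not support them.

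- **That the plan promises 90% for Helsingborg.** The text never attaches the figure to that cohort. A reader may infer it because the figure follows the change of split without qualification, but it is an inference.
- **That 90% requires 300 patients.** The article calls 300 sufficient. By Hanley–McNeil, 90% is first reached at about 250 or 314, depending on which class is the event. The value of 200 lies below both.
- **That the 79% joint probability measures damage from the re-split.** The intended design had 81%, and the article states no requirement that both cohorts succeed.
- **That a validation conclusion is put at risk.** The value 0.70 appears only in the sample-size sentence. The primary endpoint (Section 2.9.1) sets no AUC threshold, and Section 3.1 speaks only of a satisfactory level. The target also concerns the point estimate, so a confidence limit falling below 0.70 breaches nothing in the plan.
- **That a combined analysis is ruled out.** Separate assessment is stated. A pooled analysis is not described in the article, but it is not excluded either.
- **That Helsingborg alone tests transfer to another site.** The model was developed at Lund, and Section 3.1 counts both cohorts as external, although Section 2.1 labels Malmö the temporal cohort.

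It might also be said that such detail belongs in the full protocol or analysis plan. But this article itself states an operating characteristic, for a cohort size that neither cohort has.

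**Conclusion.** The point holds as a failure to update a correct figure. On the plan's assumptions (true AUC 0.74, two-thirds node-negative, normal approximation), the probability of an observed AUC of at least 0.70 is about 85–87% for the geographical cohort and about 93% for the temporal cohort. No method tried brings 200 patients within 2 points of 90%.

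Severity is minor to moderate. The loss in the smaller cohort is 3–5 points, the larger cohort gains about 3, and the chance that both reach the target hardly changes. The results do not show that the study is too small for its purpose or that its validation is unsound.

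**What to change.** In Section 2.6, keep the derivation of 300 as the intended size per cohort. After the sentence on the 400/200 split, add the probability of an observed AUC of at least 0.70 for each cohort at its actual size: about 85% at n = 200 and about 93% at n = 400, or the sponsor's own simulated values. Give the expected 95% half-widths beside them (about 0.075 and 0.053), and state that the 90% figure does not apply to the geographical cohort. If a joint probability is given, show 79% next to the 81% of the intended split.

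A pooled AUC over all 600 patients, stratified by site, is an optional supplement. It should not become the new home for the 90% statement, which was calculated for cohorts assessed separately.

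The cost is a few sentences. The sponsor's simulations already relate sample size to standard error, so no new patients or data are needed. The only drawback is that the figure quoted for the geographical cohort becomes less favourable.

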## Abstract

Newly diagnosed breast cancer (BC) patients with clinical T1–T2 N0 disease undergo sentinel-lymph-node (SLN) biopsy, although most of them have a benign SLN. The pilot noninvasive lymph node staging (NILS) artificial neural network (ANN) model to predict nodal status was published in 2019, showing the potential to identify patients with a low risk of SLN metastasis. The aim of this study is to assess the performance measures of the model after a web-based implementation for the prediction of a healthy SLN in clinically N0 BC patients. This retrospective study was designed to validate the NILS prediction model for SLN status using preoperatively available clinicopathological and radiological data. The model results in an estimated probability of a healthy SLN for each study participant. Our primary endpoint is to report on the performance of the NILS prediction model to distinguish between healthy and metastatic SLNs (N0 vs. N+) and compare the observed and predicted event rates of benign SLNs. After validation, the prediction model may assist medical professionals and BC patients in shared decision making on omitting SLN biopsies in patients predicted to be node-negative by the NILS model. This study was prospectively registered in the ISRCTN registry (identification number: 14341750).

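### The only formal calibration test named, Hosmer–Lemeshow, usually misses moderate miscalibration at n = 200 and 400 and shows neither direction nor size, so a non-significant result cannot be read as good calibration

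*Protocol article*

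**What the plan says.** Section 2.1 sets out to "evaluate the discrimination and calibration of the NILS prediction model while following the TRIPOD statement". Section 2.6 gives the content of the calibration part as "comparison of the observed and predicted event rates of benign axillary nodal status, Hosmer–Lemeshow test". That phrase holds two elements: a comparison of event rates and one named test. The Abstract repeats the first element within the primary endpoint ("compare the observed and predicted event rates of benign SLNs") and does not mention the test.

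On sample size, Section 2.6 states that "although each validation cohort will be assessed separately, the total number would be *n* = 600", and then that "we will include *n* = 400 from the temporal cohort and *n* = 200 from the geographical cohort". Separate analyses by type of breast surgery are also planned. The sample size is justified by the AUC alone. The article gives no number of groups, degrees of freedom, significance level or tolerance for the calibration assessment.

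**The concern.** The NILS output is a probability of healthy nodes, intended to support a shared decision on omitting sentinel-node biopsy (Abstract and Section 3.1). What a user needs from calibration is the direction and size of any error, because probabilities of N0 that are too high and too low have opposite consequences. The Hosmer–Lemeshow statistic sums squared deviations over risk groups, so its p-value carries neither.

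The test also has limited power in cohorts of this size. If a non-significant p-value were reported as adequate calibration, that conclusion would largely reflect the number of patients, most of all in the 200-patient cohort and in the surgery subgroups.

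**Working it through.** **Inputs from the article.** Cohorts of 400 and 200, assessed separately (Section 2.6). AUC 0.74: "The area under the curve (AUC) for the original prediction model was 0.74 in a development cohort", "where two-thirds of the patients were node-negative" (Section 2.6). About 80% node-negative among patients having sentinel-node surgery (Introduction).

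**Assumptions not in the article.** Ten equal-sized risk groups, two-sided 5% level, normally distributed linear predictor, and the sizes of miscalibration.

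**Step 1: the article's own figure.** It gives no calibration figure. Its only power statement is a 90% probability of an AUC estimate of at least 0.70 with 300 patients. With a 100/200 split, the Hanley–McNeil standard error at AUC 0.74 is 0.0285 to 0.0319, depending on which class is the event. Then Φ(0.04/0.0319) = 0.895 and Φ(0.04/0.0285) = 0.920. The 90% is reproduced, and it concerns discrimination only.

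**Step 2: the test.** H = Σ (O_g − E_g)² / [E_g(1 − E_g/n_g)], summed over g groups. The web-implemented model is applied unchanged, so nothing is fitted in the validation data and the reference distribution is χ² with g degrees of freedom (here 10). With g − 2 = 8 degrees of freedom, the type I error would be P(χ²₁₀ > 15.51) = 0.115. Simulation gave 11–12%.

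**Step 3: power at 80% N0.** A linear predictor with mean 1.63 and SD 0.957 gives 80% N0 and AUC about 0.74. The comparator is a 2-df test of calibration intercept 0 and slope 1. Each scenario used 1,000 to 4,000 replicates.

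| Miscalibration | Hosmer–Lemeshow, n = 200 / 400 | 2-df test, n = 200 / 400 |
|---|---|---|
| None | 5% / 6% | 5% / 5% |
| N0 under-predicted by about 5 points (mean predicted 75.4%, true 80%) | 6% / 16% | 28% / 55% |
| N0 over-predicted by about 5 points | 25% / 42% | 29% / 52% |
| N0 over-predicted by exactly 5 points (predicted 80%, true 75%) | 30% / 48% | 35% / 65% |
| Calibration slope 0.7 | 22% / 33% | 24% / 44% |
| N0 over-predicted by 10 points | 81% / 98% | 90% / >99% |
| N0 under-predicted by 10 points (predicted 70%, true 80%) | 47% / 92% | 89% / >99% |
| Predicted 66.8%, true 80% | 83% / 99.8% | not needed |

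The two rows marked about 5 points use a logit shift of about 0.3, or roughly 4.5 points. Repeated runs differ by a point or two. At n = 200, Hosmer–Lemeshow rejects the 5-point under-prediction hardly more often than a perfectly calibrated model.

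**Step 4: sensitivity, two-thirds N0.** Hosmer–Lemeshow power at n = 200 / 400 is 9% / 20% for a 5-point under-prediction, 20% / 35% for a 5-point over-prediction, 23% / 38% for slope 0.7 and 65% / 93% for a 10-point over-prediction.

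**Step 5: what estimates would deliver.** Simulated standard errors, with 95% half-widths of 1.96 × SE:

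| | n = 200 | n = 400 |
|---|---|---|
| Observed minus predicted rate, 80% N0 | 0.026, ±5 points | 0.019, ±4 points |
| Observed minus predicted rate, two-thirds N0 | 0.030, ±6 points | 0.022, ±4 points |
| Slope, 80% N0 | 0.23, ±0.45 | 0.16, ±0.31 |
| Slope, two-thirds N0 | 0.20, ±0.39 | 0.14, ±0.27 |

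**The case against.** The strongest reply is that the article does not rely on Hosmer–Lemeshow alone. The same phrase in Section 2.6, and the Abstract, plan an observed-versus-predicted comparison, which can show direction and size. In the 5-point under-prediction scenario, a simple z-test on observed minus predicted events has 34% / 62% power at n = 200 / 400, no worse than the 2-df test. This stands: a reader might infer that calibration rests entirely on the test, and the text does not support that. What remains is that the form of the comparison is open while the one formal test named is a weak one.

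A reader might also infer that moving from a development cohort with two-thirds N0 to a population with 80% N0 would go unnoticed. A full shift of that size would normally be caught, with 83% power at n = 200 and 99.8% at n = 400. Only partial shifts of about 5 points are usually missed.

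The article does not state 8 degrees of freedom or ten groups, so the inflated type I error is a hazard to avoid and not an error in the plan. Intercept, slope and curve may be specified in a full protocol or SAP that is not shown, so their absence is not the point.

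Finally, part of the low power is sample size. For over-prediction and for slope 0.7 at n = 200, the 2-df test gains only a few points. This also stands.

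**Conclusion.** The point holds in a limited form. The named test gives no direction or size, and in separately assessed cohorts of 200 and 400 it usually misses moderate miscalibration: power about 6% / 16% for under-prediction of N0 by about 5 points, 25% / 42% for over-prediction by about 5 points, and 22% / 33% for slope 0.7. Errors of 10 points or more are usually detected, except that a 10-point under-prediction at n = 200 is close to even odds (47%). A non-significant result is therefore not evidence of good calibration.

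The figures rest on 10 groups, 10 degrees of freedom, AUC about 0.74, 80% N0 and a normal linear predictor. With two-thirds N0 the conclusion is the same. It does not follow that the study has no means of seeing miscalibration, because the planned comparison of rates could supply it once its form is fixed.

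**What to change.** In Section 2.6 or the SAP, replace Hosmer–Lemeshow as the basis for the calibration conclusion. For each cohort, report:

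- the calibration intercept with the slope held at 1, with a 95% confidence interval, alongside observed minus predicted N0 in percentage points;
- the calibration slope with a 95% confidence interval;
- a calibration curve.

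This gives the planned observed-versus-predicted comparison a definite form. If Hosmer–Lemeshow is kept, label it descriptive, use g degrees of freedom, and state that a non-significant result will not be read as good calibration.

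The cost is a wording change and a few lines of code, with no new data. The intervals will remain wide at n = 200, and the report should say so.
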